### Interventions

#### Internet-delivered psychological intervention

All interventions (except iTAU) comprise two face-to-face individual sessions and 6 online, individual and interactive therapeutic modules. Each face-to-face session will be 90 min in length. The online therapeutic modules are oriented to work on different psychological techniques, supported by multimedia material (videos, audio, etc.), as Internet support, and the duration of each module will be approximately 60 min.

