#### Descriptions of costing procedure

Data collection on the use of health and social services will be collected through the CSRI-Spanish version [39, 50]. Costs of the study will be estimated from the healthcare and societal perspectives during the previous six months (before baseline), and during the six months of follow-up. Direct health care costs will be calculated by adding the costs derived from pharmacological consumption, use of health services and clinical tests, and costs incurred by the staff running the intervention.

The cost of medication will be calculated by determining the price per milligram during the study, according to the databases of the Spanish Ministry of Health and Consumer Affairs, including value-added tax. The total cost of medication will be calculated by multiplying the price per milligram by the daily dose in milligrams and the number of days of treatment. The main source of the unit cost data for medical tests and health services is the OBLIKUE database of health care costs [54]. The OBLIKUE database contains information about Spanish health service costs and is derived by systematic reviews of the literature. Indirect costs (lost productivity) will be calculated considering sick leave days and multiplying them by the minimum daily wage in Spain for 2018. Finally, total costs will be calculated by adding direct and indirect costs. The unit costs will be expressed in euros (€), based on 2018 prices.

The two interventions in this study will be conducted by government agencies and financed by the Carlos III Health Institute; their implementation will not incur additional costs for the Spanish National Health Service. Therefore, costs associated with the interventions in the study will not be included.

The economic evaluation of this study will follow the general guidelines for conducting pharmacoeconomic analyses in Spain. It will also follow the Guidelines of the International Society for Pharmacoeconomics and Outcomes Research (ISPOR) [55] and the Consolidated Health Economic Evaluation Reporting Standards (CHEERS) [56].

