#### Utility scores

Utility scores will be obtained from two health-related quality of life questionnaires EuroQol 5D and SF-12. QALYs will be calculated based on these scores using the Spanish EQ-5D tariffs [57]. Along with EQ-5D utility scores, scores recorded on the EQ VAS will also be used as an outcome for the analysis.

The perspective used in our analysis will be twofold: the social perspective, to include all costs and quality of life, and the perspective of the Spanish health system.

The time horizon of the study is six months, so it will not be necessary to apply a discount factor to the costs.

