#### Cost-utility analysis

Cost-effectiveness will be explored through the calculation of incremental cost-effectiveness ratios (ICERs) for the intervention group using the iTAU group as the control. To estimate the ICER (ratio between incremental costs and incremental effectiveness) the following equation will be used:$$ ICER=\frac{Cost\kern0.17em active\kern0.17em intervention\ group\hbox{-} Cost\ control\ intervention\ group}{Effectiveness\ or\ Utility\ active\ intervention\ group\hbox{-} Effectiveness\ or\ Utility\ control\ intervention\ group\ } $$

Cost-utility will be explored through the calculation of incremental cost-utility ratios (ICURs), which are defined as the ratio between incremental costs and incremental effects measured on QALYs [58]. QALYs will be approximated by using the area-under-the-curve technique.

Data collection will be performed using Excel software and statistical analysis will use SPSS (SPSS Inc., Chicago, IL, USA) software version 20, licensed by the University of Malaga.

Frequency and proportions will be used for descriptive statistics of categorical or qualitative variables. For quantitative variables, the mean and standard deviation will be obtained.

Inferential statistical analysis will use the Chi-square test for qualitative variables, one-way ANOVA test for qualitative and quantitative variables and Student’s t-test for quantitative variables. In all cases, statistical significance will correspond to a value of *p* < 0.05.

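### The costing section both counts and excludes intervention costs; if the exclusion is followed, incremental cost is understated by the full cost of the programme

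*Protocol article*

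**What the plan says.** Under Descriptions of costing procedure, direct health care costs are the sum of drug costs, "use of health services and clinical tests, and costs incurred by the staff running the intervention". In the same section, after the paragraph on unit costs, the article says that the two interventions are run by government agencies and paid for by a public research funder, and that "their implementation will not incur additional costs for the Spanish National Health Service". It then concludes: "Therefore, costs associated with the interventions in the study will not be included".

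Utility scores sets two perspectives: "the social perspective, to include all costs and quality of life, and the perspective of the Spanish health system". Cost-utility analysis defines the comparison as "incremental cost-effectiveness ratios (ICERs) for the intervention group using the iTAU group as the control", and the ICUR as incremental cost over incremental QALYs.

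The Interventions section gives the two face-to-face sessions and six online modules to the intervention arm only: "Each face-to-face session will be 90 min in length". Improved usual care, including the GP training, goes to everyone. Under Ethical aspects, control patients may take the programme only once the study has ended.

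**The concern.** The two costing rules are opposites and the article does not say which one holds. With both in place, the rule could be chosen after the cost data have been seen.

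The choice matters because improved usual care is common to both arms. Leaving out the cost of both interventions therefore does not cancel between arms; it removes programme delivery from one side of the difference. The reason given is who pays during the trial. That does not make therapist time free to society, and it does not answer what the programme would cost in routine care. The Discussion names cost-effectiveness for the Spanish National Health System as an aim, with results meant to inform guidelines, so the cost of routine delivery is the relevant one.

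**Working it through.** The costing section gives no unit cost, programme cost or expected QALY gain, so there is no plan figure to reproduce. The check sets the passages side by side and then works out the size under stated assumptions.

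**Which rule gives what**

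| Rule followed | Therapist time | Platform and support | Consistent with all costs (societal)? |
|---|---|---|---|
| Direct-cost definition | Counted | Not named in the list | Only if platform and support are added |
| Exclusion sentence | Zero | Zero | No |

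**Effect on the ratio**

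Let C be the programme cost per participant, ΔK the difference in all other costs, and ΔE the difference in effect or QALYs.

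- Full ratio: (ΔK + C) / ΔE
- Ratio under the exclusion: ΔK / ΔE
- Shift: −C / ΔE

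Incremental cost is too low by exactly C. With ΔE > 0 the ratio is too low by C / ΔE. Net monetary benefit is λΔE − (ΔK + C), with λ the value placed on a QALY. Dropping C raises it by C whatever the sign of ΔE.

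**Inputs from the article**

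- Two face-to-face sessions of 90 min (Interventions)
- 150 participants per arm (Randomization, allocation and masking)

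**Scheduled contact time**

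- Per participant: 2 × 1.5 h = 3 h
- Intervention arm, all attending both sessions: 3 h × 150 = 450 h

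This is a ceiling for face-to-face time. The second session is listed after module 5, so early dropouts would miss it. If everyone attended session 1 and 30% (the dropout rate aimed for in the Discussion) missed session 2, the total would be 150 × 1.5 + 105 × 1.5 = 382.5 h, or 2.55 h per participant.

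**Cost, at an assumed EUR 20-60 per staff hour**

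- Per participant: 3 × 20 = EUR 60 to 3 × 60 = EUR 180
- Intervention arm in total: 450 × 20 = EUR 9,000 to 450 × 60 = EUR 27,000
- With 2.55 h instead: EUR 51 to EUR 153 per participant

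Platform hosting, maintenance and support would come on top.

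**Shift in the ICUR, for an assumed gain of 0.01-0.03 QALY and full attendance**

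| C per participant | Gain 0.03 | Gain 0.01 |
|---|---|---|
| EUR 60 | 2,000 | 6,000 |
| EUR 180 | 6,000 | 18,000 |

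(EUR per QALY; each cell is C divided by the gain.)

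**The case against.** Five points can be made on the other side.

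- **The bias is conditional.** A reader might infer that the ICER and ICUR are certain to omit the programme cost. The documents do not support that: if the direct-cost definition governs, staff time is counted. This stands. What is established is two incompatible rules, one of which omits the cost.
- **No cost figure shows that this is the main difference between arms, or that the programme would look dominant.** Drugs, service use, tests and sick leave are also costed and could differ by more. This stands. The documents support only that the programme is the one resource assigned by design to a single arm.
- **The euro figures rest on assumptions.** The hourly rate and the QALY gain are both assumed, and the widest range pairs opposite extremes. This stands. The figures show scale and do not prove materiality.
- **The exclusion is arguable for the health service during the trial.** If a research funder pays, the service's in-trial budget is unaffected. This stands only as a narrow budget view. It cannot justify the exclusion for the societal analysis, and it does not describe routine delivery.
- **The economic analysis is not the primary outcome.** The main hypothesis, primary outcome and sample size are clinical. This stands and lowers the severity, but it leaves the contradiction in place.

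The article's condensed form is no defence, since it states both rules outright.

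**Conclusion.** The costing section contradicts itself, and its exclusion sentence contradicts the societal perspective. If that sentence is followed, incremental cost is understated by the full programme cost and net benefit is overstated by the same amount. The ratio itself moves in the programme's favour only if the incremental effect is positive.

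The documents fix the size only in time: 3 h of scheduled contact per participant, at most 450 h in the intervention arm. The money figures (up to EUR 60-180 per participant before platform costs, and EUR 2,000-18,000 per QALY) depend wholly on the assumed hourly rates and QALY gains.

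This should be fixed, but it ranks below defects that threaten the primary result, because randomization and the clinical efficacy analysis are untouched.

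**What to change.** - Delete the exclusion sentence so that the rule counting intervention staff stands.
- Include delivery costs in the base case of both perspectives: session time × unit cost, plus platform hosting, maintenance and support per user. In the health-system analysis, describe them as the cost of routine delivery.
- Leave out research-only and one-off development costs, and say so.
- If a version without programme costs is wanted, as the in-trial health-service budget view, present it only as a labelled sensitivity analysis.

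The cost is a change of wording and a short log of staff hours and hosting cost, most easily kept as the trial runs. The design does not change. The downside for the sponsor is a less favourable ICER than the exclusion would give.

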#### Utility scores

Utility scores will be obtained from two health-related quality of life questionnaires EuroQol 5D and SF-12. QALYs will be calculated based on these scores using the Spanish EQ-5D tariffs [57]. Along with EQ-5D utility scores, scores recorded on the EQ VAS will also be used as an outcome for the analysis.

The perspective used in our analysis will be twofold: the social perspective, to include all costs and quality of life, and the perspective of the Spanish health system.

The time horizon of the study is six months, so it will not be necessary to apply a discount factor to the costs.

#### Cost-utility analysis

Cost-effectiveness will be explored through the calculation of incremental cost-effectiveness ratios (ICERs) for the intervention group using the iTAU group as the control. To estimate the ICER (ratio between incremental costs and incremental effectiveness) the following equation will be used:$$ ICER=\frac{Cost\kern0.17em active\kern0.17em intervention\ group\hbox{-} Cost\ control\ intervention\ group}{Effectiveness\ or\ Utility\ active\ intervention\ group\hbox{-} Effectiveness\ or\ Utility\ control\ intervention\ group\ } $$

Cost-utility will be explored through the calculation of incremental cost-utility ratios (ICURs), which are defined as the ratio between incremental costs and incremental effects measured on QALYs [58]. QALYs will be approximated by using the area-under-the-curve technique.

Data collection will be performed using Excel software and statistical analysis will use SPSS (SPSS Inc., Chicago, IL, USA) software version 20, licensed by the University of Malaga.

Frequency and proportions will be used for descriptive statistics of categorical or qualitative variables. For quantitative variables, the mean and standard deviation will be obtained.

Inferential statistical analysis will use the Chi-square test for qualitative variables, one-way ANOVA test for qualitative and quantitative variables and Student’s t-test for quantitative variables. In all cases, statistical significance will correspond to a value of *p* < 0.05.

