The content of the modules is explained in depth later. The structure of the modules always follows the same scheme: each begins with the explanation of the contents of the module, different exercises are proposed, and then the self-test questions are presented to verify whether the explanation has been understood. If any user does not correctly answer any question, the computer program will immediately provide the correct feedback with a simple explanation. The module ends with the proposal of homework with the aim of practising what has been learned. In addition, before starting each module, a check is made to see whether the participants have carried out the proposed tasks and responds by congratulating them or encouraging them to do the task. It is very important to carry out these tasks in order to consolidate everything learned in the programme and so that the strategies offered by the programme are turned into skills. An important aspect is the possibility of reviewing the content of the different modules. The programme is designed to last 8–12 weeks. After some time without accessing the computer program (a time that can be programmed), the user will receive a reminder e-mail to continue completing the modules. The clinician can modify the period that should pass without entering to receive said reminder. The programme contents are the following:*Face-to-face session 1. Presentation of the programme:* Motivational techniques will be used to increase adherence of participants to face-to-face sessions and homework, and adherence to pharmacological treatment will be also promoted as one of the main focal points of the programme. The online computer program will be presented and patients will be trained in the procedure to log in and use it from home.*M1. Psychoeducation of depression:* The impact of depression on patients’ quality of life and functional ability, as well as on the prognosis of diabetes and other chronic diseases, will be described. The initial symptoms of depression and how to respond when they appear will be analysed. Self-control under stress will be emphasized, with patients taught to do relaxation exercises and to reward efforts and achievements made. In addition, specific techniques and very useful and practical tips to reduce stress in daily life will be explained.*M2. Healthy Life Style*: The need to carry out regular physical activity will be explained. The Mediterranean diet will be introduced, with education on the need to follow 6 healthy dietary commands. All of this will come with information and practical exercises on how to systematize food-related behaviours. Developing a social support network will be emphasized. People will be shown specific techniques on how to create and maintain an adequate social support network.*M3. Behavioural activation:* The importance of establishing and maintaining an adequate level of activity and involvement with life will be considered. Patients will be taught to schedule activities, and the need to monitor the performance of significant activities will be explained. The essential tool of this module will be the ‘Activity Diary’.*M4. Positive psychology:* This module will help patients to see the importance of positive emotions and learn procedures that generate positive experiences, encouraging involvement in pleasant and meaningful activities and contact with other people.*M5. Mindfulness and compassion*: This module will include components of Mindfulness-based Cognitive Therapy (MBCT). Core mindfulness practices will be carried out: the practice of breathing, the body scan and the 3-min exercise. The importance of establishing a regular mindfulness practice, as well as regular informal practice, will be considered. Some basic elements of compassion will be included, such as the self-compassionate pause.*Face-to-face session 2. Review of completed modules already and practice*. This is a structured session comprising: a) resolution of doubts, b) performing some of the most important practices (proposed to be done periodically at home), c) emphasizing the continuous putting into practice of the strategies learned and d) farewell and intervention closure.*M6. Relapse prevention and maintenance*: This module aims to strengthen the strategies learned during the programme. The possibility of continuing to practice the strategies learned once the treatment is completed will also be discussed, with emphasis on the fact that participants can continue to use the online computer program during the entire follow-up period (6 months) for this purpose. It will also teach participants how to identify and cope with future high-risk situations. Finally, instructions will be given to conduct follow-up evaluations.

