### Instruments

The assessor will be blind to the type of treatment that will be administered to patients. In addition, this assessor will be different from the person who collects the measurements of the study results. As far as possible, GPs will also be blind to the intervention arm to which each patient is allocated, since their intervention should be based only on usual practice, based on the criteria set out in the Guide for the Treatment of Depression in Primary Care.

Patients will be assessed at baseline (post-randomization), after the treatment, and at 3-month and 6-month follow-ups, in order to test whether the improvements achieved during the therapy are maintained in the long term. The study variables assessed are summarized in Table 2. The study flowchart is shown in Fig. 1.

**Table 2 Tab2:** Study variables

Instrument	Assessment area	Time to assessment	Applied by
PHQ-9 (40, 41)	Severity of depression	Baseline and follow-up sessions^a^	Researcher A phone Online (follow-up sessions^a^)
Glycosylated haemoglobin	Diabetes control	Baseline and follow-up sessions^a^	Online
FPS-R [42]	Pain intensity	Baseline and follow-up sessions^a^	Online
Roland-Morris Scale [43–46]	Physical limitation	Baseline and follow-up sessions^a^	Online
MINI [47]	Psychiatric diagnosis	Baseline	Researcher A phone
Sociodemographic data	Gender, age, marital status, education, occupation, economical level	Baseline	Researcher A phone
SF-12 Health Survey [48, 49]	Health-related quality of life	Baseline and follow-up sessions^a^	Online
CRSI [39, 50]	Health and social services use	Baseline and 6 months post-treatment	Researcher A phone (Baseline) Researcher B phone (6 months post-treatment)
EQ-5D-3 L [51, 52]	Quality of life related to health	Baseline and follow-up sessions^a^	Online
OFS [53]		Baseline and follow-up sessions^a^	Online

*PHQ-9* Patient Health Questionnaire, *FPS-R* Faces Pain Scale –Revised, *MINI* Mini-International Neuropsychiatric Interview, *CSRI* Client Service Receipt Inventory, *EQ-5D-3 L* EuroQol-5D-3 L, *OFS* Openness to the Future Scale

^a^Follow-up sessions: post-treatment, 3 and 6 post-treatment months

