### Analysis strategy

#### Analysis of clinical efficacy

Intention-to-treat and per-protocol analysis will be used. Analysis will include the description and ‘head-to head’ comparison between the two groups. Descriptive statistics of the included variables (mean and 95% confidence interval for normally distributed quantitative variables; and median and interquartile range for abnormally distributed quantitative variables) will be performed. To confirm the main hypothesis, all variables will be compared (t0-tk) using an analysis of variance (ANOVA) and post-hoc tests or Kruskal-Wallis non-parametric tests. Finally, more sophisticated multivariate analysis, including multilevel regression, will be used. The effect size of improvement and the number needed to treat (NNT) in each arm will be estimated.

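### The cost-utility section names only unadjusted comparisons for the QALY difference; adjusting for baseline EQ-5D utility, already collected, would improve precision at no cost

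*Protocol article*

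**What the plan says.** All references are to the protocol article.

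- **QALY construction.** Under Cost-utility analysis, "QALYs will be approximated by using the area-under-the-curve technique".
- **Incremental measure.** The same section defines ICURs as ratios, "which are defined as the ratio between incremental costs and incremental effects measured on QALYs". The equation printed for the ICER divides the difference in group costs by the difference in group effectiveness or utility. No covariate appears in it.
- **Inference.** The section ends with a list of tests: chi-square, then "one-way ANOVA test for qualitative and quantitative variables and Student’s t-test for quantitative variables".
- **Regression elsewhere.** Analysis of clinical efficacy says that "more sophisticated multivariate analysis, including multilevel regression, will be used". It lists no covariates and does not mention QALYs.
- **Utility measurements.** Under Instruments, "Patients will be assessed at baseline (post-randomization), after the treatment, and at 3-month and 6-month follow-ups". Table 2 has the EQ-5D-3L at all four times.
- **Timing.** On the online intervention, "The programme is designed to last 8–12 weeks". Utility scores gives a six-month time horizon but does not say when it begins.

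**The concern.** A patient's utility before treatment predicts that patient's utility later. If one arm happens to start higher, it will tend to accrue more QALYs whatever the treatment does. There are two routes. If the curve starts at baseline, the baseline value has its own weight in the first trapezoid. Whether or not it does, part of the imbalance persists at later visits.

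The QALY difference is the denominator of the ICUR and is likely to be small over so short a horizon, so a small absolute shift can be a large relative one. Cost-effectiveness is a declared aim of the trial (Discussion). The baseline EQ-5D that would absorb most of this noise is already in the data, and the methods named in the section leave it unused.

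**Working it through.** The plan states no figure for QALYs, utility SD or correlation, so there is nothing of its own to reproduce here.

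**Inputs from the document.** 150 patients per arm (Randomization, allocation and masking of study groups); EQ-5D at baseline, post-treatment, and 3 and 6 months later (Table 2); programme length 8–12 weeks.

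**Assumptions.** Utility SD 0.25 at every visit; correlation ρ between any two visits, equal for all pairs, from 0.4 to 0.7; visits at 0, 0.20, 0.45 and 0.70 years (treatment of about 10 weeks).

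**1. Chance imbalance at baseline.** SE = SD × √(2/n) = 0.25 × √(2/150) = 0.029. The 95% range is ±1.96 × 0.0289 = ±0.057. An imbalance of 0.05 is 0.05/0.0289 = 1.73 SE.

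**2. Trapezoid weights (years).** Baseline 0.20/2 = 0.100; post-treatment (0.20 + 0.25)/2 = 0.225; 3 months (0.25 + 0.25)/2 = 0.250; 6 months 0.25/2 = 0.125. The sum is 0.70, and the baseline share is 0.100/0.70 = 14%. For programmes of 8 and 12 weeks the share is 0.077/0.654 = 12% and 0.115/0.731 = 16%.

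**3. Carry-over per unit of baseline difference.** Slope = 0.10 + ρ × (0.225 + 0.250 + 0.125) = 0.10 + 0.6ρ.

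| ρ | Slope | Shift from a 0.05 imbalance (QALY) |
|---|---|---|
| 0.4 | 0.34 | 0.017 |
| 0.5 | 0.40 | 0.020 |
| 0.6 | 0.46 | 0.023 |
| 0.7 | 0.52 | 0.026 |

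Of each shift, only 0.10 × 0.05 = 0.005 comes through the first trapezoid; the rest comes through correlation.

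**4. Comparator.** A true gain of 0.05 at all three later visits is worth 0.05 × 0.6 = 0.030 QALY. The shift is 0.017/0.030 = 57% to 0.026/0.030 = 87% of that.

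**5. Variance removed by adjustment.** R² = slope² / (w′Rw), with w the weights and R the correlation matrix. For ρ = 0.4, w′Rw = 0.279 and R² = 0.34²/0.279 = 0.41. For ρ = 0.7, w′Rw = 0.385 and R² = 0.52²/0.385 = 0.70. At ρ = 0.5, R² = 0.40²/0.314 = 0.51, and the SE of the QALY difference falls from 0.0162 to 0.0113.

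**6. Sensitivity to the correlation pattern.** If correlation decays visit by visit (ρ, ρ², ρ³), R² is 0.23 at ρ = 0.4 and 0.51 at ρ = 0.7.

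**7. Sensitivity to the start of the horizon.** If the six months begin after treatment, the weights are 0.125, 0.250 and 0.125, and baseline has weight 0. The slope is 0.5ρ, so a 0.05 imbalance shifts the difference by 0.010 (ρ = 0.4) to 0.0175 (ρ = 0.7). Under equal correlation, R² is 0.20²/0.156 = 0.26 to 0.35²/0.203 = 0.60.

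**The case against.** The document nowhere says that QALYs will be compared without adjustment. An area-under-the-curve QALY can be analysed with a baseline covariate, and adjusted means fit the printed ratio as well as raw means do. The list of tests is sorted by variable type and does not name QALYs. The economic evaluation is also to follow ISPOR, CHEERS and Spanish guidelines. An article can leave a covariate list to a separate plan, so its absence alone would be no finding.

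This limits the point but does not remove it. The section goes beyond silence: it prints a difference of group values and names tests of which none takes a continuous baseline covariate. The regression is named only under clinical efficacy. A general commitment to guidelines does not replace the specific methods listed.

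Three stronger readings are tempting, and the document does not support them:

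- **That the planned QALY comparison is biased.** Under randomisation it is unbiased. What remains is imbalance in the realised sample and lost precision.
- **That a baseline difference passes straight into the QALY difference.** The document does not say that the curve starts at baseline. If it does, baseline has about 12–16% of the weight; if the six months start after treatment, it has none.
- **That a modest imbalance could double, erase or reverse the result.** To cancel or double 0.030 QALY takes an imbalance of 0.030/0.52 = 0.058 to 0.030/0.34 = 0.088, just outside to well outside the ±0.057 range. A smaller true effect would be more exposed, but the document gives no expected QALY effect.

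**Conclusion.** The point holds as a free improvement. Every comparison that the cost-utility section names is unadjusted, and using baseline utility would be better with data already in hand. On the illustrative assumptions, a 0.05 imbalance moves the QALY difference by 0.017–0.026, and adjustment removes about 41–70% of its variance. That variance figure depends on equal correlation between visits. It drops to about 23–51% with decaying correlation, and to about 26–60% if the horizon starts after treatment. The direction of the gain is the same in every case examined. The exact size is uncertain, because the SD, correlations and visit times are all assumed.

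**What to change.** In the Cost-utility analysis section, state that the QALY difference will be estimated by linear regression of area-under-the-curve QALYs on arm, baseline EQ-5D utility and centre, and that this adjusted difference is the denominator of the ICUR. Add when the six-month horizon starts, so that it is clear whether the baseline value is part of the curve or only a covariate.

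The Instruments section labels baseline as after randomisation, while the section on randomisation has baseline data collected before allocation is requested. The text should therefore also say that the covariate is the utility recorded before the patient learns the allocation.

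The cost is a few sentences of analysis wording. No extra data, visits or patients are needed.

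### The tests named in the cost-utility section cannot quantify uncertainty for the ICER or ICUR; a joint cost–effect method should be added

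*Protocol article*

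**What the plan says.** All of the following stands under Cost-utility analysis in the protocol article.

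- The cost-effectiveness measure: "Cost-effectiveness will be explored through the calculation of incremental cost-effectiveness ratios (ICERs) for the intervention group using the iTAU group as the control". An equation gives it as the difference in cost divided by the difference in effectiveness or utility.
- The cost-utility measure is the same ratio with QALYs in the denominator, and "QALYs will be approximated by using the area-under-the-curve technique".
- Descriptive statistics, after a statement about software: "For quantitative variables, the mean and standard deviation will be obtained".
- Inference: "Inferential statistical analysis will use the Chi-square test for qualitative variables, one-way ANOVA test for qualitative and quantitative variables", followed by "Student’s t-test for quantitative variables".
- The criterion: "In all cases, statistical significance will correspond to a value of" p < 0.05.

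Two other places bear on the point. Descriptions of costing procedure commits the evaluation to Spanish pharmacoeconomic guidance, ISPOR and CHEERS. Analysis of clinical efficacy has its own methods (ANOVA, Kruskal-Wallis, multilevel regression).

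**The concern.** The quantity of interest is a ratio of two between-arm differences, measured on the same patients and therefore correlated. A chi-square test, ANOVA or t-test examines one variable at a time. It yields neither an interval for the ratio nor any use of the covariance between cost and QALYs. The named inference therefore does not fit the section's own estimand.

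The Discussion gives cost-effectiveness as an aim alongside effectiveness. A decision-maker needs to know how uncertain the ratio is and how probable it is that the programme is worth its cost at a given threshold. A point ratio with p-values for single variables answers neither question.

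**Working it through.** **The plan's own figures.** The economic section states no number, interval or power. The sample size supplies only the number per arm. For 0.5 SD, 80% power and two-sided 5%: n = 2(1.96 + 0.8416)²/0.5² = 62.8, so 63 per group. Four groups give 252, and 252/0.85 = 297 against the stated 300. This reproduces, and 252/2 = 126 analysed per arm is used below.

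**Assumed inputs.** Cost SD (sC), QALY SD (sQ), their correlation ρ and the threshold λ are not in the documents. All values below are assumptions and show sensitivity only.

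**Step 1: what the covariance does.** Incremental net benefit is λ·ΔQ − ΔC, with

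SE² = (2/n)(λ²sQ² + sC² − 2λρ·sC·sQ).

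Relative to ρ = 0, the SE is multiplied by √(1 − ρw), where w = 2λ·sQ·sC/(λ²sQ² + sC²).

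| λ, sQ | sC | w | ρ = -0.4 | ρ = +0.4 |
|---|---|---|---|---|
| €25,000, 0.12 | €1,000 | 0.600 | 1.11 | 0.87 |
| €25,000, 0.12 | €2,000 | 0.923 | 1.17 | 0.79 |
| €25,000, 0.12 | €3,000 | 1.000 | 1.18 | 0.77 |
| €20,000, 0.10 | €1,000 | 0.800 | 1.15 | 0.82 |
| €20,000, 0.10 | €2,000 | 1.000 | 1.18 | 0.77 |
| €20,000, 0.10 | €3,000 | 0.923 | 1.17 | 0.79 |

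The effect is largest where sC = λ·sQ (w = 1). Independence is only a reference point here; the plan does not assume it.

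**Step 2: same marginal results, different economic conclusion.** Take n = 126 per arm, sC = €2,000, sQ = 0.10, λ = €20,000, ΔC = −€200 and ΔQ = 0.02. These values have w = 1, so the correlation effect is at its greatest.

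- Separate tests: SE(ΔC) = 2,000√(2/126) = 252, p = 0.43. SE(ΔQ) = 0.10√(2/126) = 0.0126, p = 0.11. Neither depends on ρ.
- Net benefit = 20,000 × 0.02 + 200 = €600 for every ρ.
- ρ = -0.5: SE 436, 95% CI −255 to 1,455, probability cost-effective 0.915.
- ρ = 0: SE 356, 95% CI −98 to 1,298, probability 0.954.
- ρ = +0.5: SE 252, 95% CI 106 to 1,094, probability 0.991.

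The same pair of p-values is compatible with a net-benefit interval that includes zero and with one that excludes it.

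**Step 3: the ratio itself.** A Fieller set is bounded only if ΔQ² − 1.96²·Var(ΔQ) > 0. Keep the SDs and n of step 2, but set ΔC = +€200.

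- ΔQ = 0.02: 0.000400 − 3.8416 × 0.0001587 = −0.00021, so the set is unbounded, although the point ratio is 200/0.02 = €10,000 per QALY.
- ΔQ = 0.03 (p = 0.017): the point ratio is €6,667. The limits are −7,714 to 91,083 at ρ = -0.5, and −26,846 to 26,172 at ρ = +0.5.

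Negative limits for a ratio are hard to read, which is a reason to report net benefit alongside it.

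**The case against.** The strongest reply is that the sentence on tests is a general statistics paragraph. It follows the software statement, assigns tests by type of variable and does not mention costs, QALYs or either ratio. A reader might infer that the plan will test costs and effects separately; the text does not say so. That part of the objection stands. It does not remove the point, because costs and QALYs are quantitative variables and fall under the rule on either reading. Clinical efficacy also has its own methods section, and nothing else is named for the economic comparison.

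A second reply is that a condensed article may leave a bootstrap or acceptability curve to the full plan, and that the evaluation is to follow ISPOR and CHEERS. Silence on a method would indeed be no fault. The finding is that the article fixes a set of tests that does not serve its estimand. A general commitment to guidance does not replace the tests that are named.

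Third, a reader might infer that skewed costs make the t-test invalid. The check does not support this. With lognormal costs at coefficients of variation 1 to 3 and 126 to 150 per arm (20,000 simulated trials each), type I error was 0.050 to 0.037. Coverage of the unequal-variance 95% interval for the mean difference was 0.948 to 0.957. The t-test compares arithmetic means, which is the relevant quantity for costs, and at this size it is near-nominal to mildly conservative.

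Fourth, the chance that the observed QALY difference falls near or below zero depends on effect, SD and sample size, not on the test chosen. It is no measure of this fault. The section also describes the ratios as something to be explored, and no alpha or sample size depends on them.

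**Conclusion.** The point holds in limited form. The univariate tests named in the cost-utility section cannot give an interval for the ICER or ICUR, or a probability of cost-effectiveness, and no other inference for them is named. It does not follow that the plan commits to separate tests on costs and effects, nor that skewness invalidates a t-test on mean costs.

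The size is not known from the documents. Over the assumed ranges in the table, the net-benefit SE relative to independence lies between 0.77 and 1.18; the widest values occur where cost SD equals threshold times QALY SD. The analysis is secondary, so the clinical conclusion, the sample size and the trial's conduct are untouched. What would be weakened is the cost-effectiveness statement.

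**What to change.** For the economic endpoints, add one joint cost–effect method to the cost-utility section:

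- a non-parametric bootstrap that resamples patient-level cost–QALY pairs within arm; or
- net-benefit regression, in which λ × QALY − cost is computed for each patient and regressed on arm, so that the covariance is carried in the individual values.

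Report the mean cost and mean QALY differences with 95% CIs, and incremental net benefit or an acceptability curve over a stated range of thresholds, for both the societal and the health-system perspective. The t-tests on mean costs may stay as descriptive comparisons.

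The cost is a little more analysis work: the bootstrap may need a short script beyond standard SPSS menus. No new data are needed.
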